### Prior Work

To establish an appropriate dosage and duration for the clinical trial, systematic research of human studies involving vitamin E supplementation in healthy participants spanning the years 1997 to 2019 was conducted. A comprehensive search using keywords such as “human,” “vitamin E,” “tocopherol,” and “tocotrienol” in the PubMed database yielded 9 published papers. These studies shed light on the dosages and durations of tocotrienols that are suitable for this clinical trial. In a comparative study investigating the impact of supplementation with TRF and αTP on gene expression in healthy older adults, the administration of αTP (400 IU/day) and TRF (150 mg/day) over a period of 6 months was found to influence pathways related to immune response, drug response, cell adhesion, and signal transduction pathways. Notably, TRF supplementation exhibited a more pronounced effect than αTP in modulating gene expression involved in signaling pathways [80]. The same study also revealed that TRF and αTP supplementation demonstrated similar antioxidative and anti-inflammatory effects in older adults, with TRF showing more significant impacts in female participants [74]. This occurrence may be associated with the downregulation of the apoptotic pathway such as ERK1/2 cascades and NF-κB pathway after 6 months of TRF supplementation [80]. Moreover, another study revealed that TRF supplementation (150 mg/day) for 6 months led to alterations in plasma protein levels including upregulation of apolipoprotein A-I and E precursors and downregulation of CRP precursors in both young and older individuals, actions that are associated with a therapeutic effect against atherosclerosis [81]. These findings provide a perspective that TRF also alters protein expression as shown by elevated plasma protein levels following 6 months of TRF supplementation.

Another investigation focused on the effects of TRF supplementation at a dosage of 400 mg/day for 2 months on the immune response to tetanus toxoid immunization in healthy volunteers. The findings indicated that TRF exhibited immunostimulatory effects [82], thus reinforcing the notion that TRF is associated with handling cellular inflammation. In a randomized controlled trial spanning 6 months, daily supplementation of 150 mg/day TRF was associated with improvements in lipid profile and oxidative status in healthy older adults [83]. Interestingly, a separate trial found that daily supplementation with TRF (150 mg/day) for 6 months did not induce immunomodulatory changes in healthy human volunteers [84]. A much earlier clinical trial, comparing 50-mg with 100-mg vitamin E supplementation over 6 months, suggested that the higher dose (100 mg) had a more pronounced effect on cellular immune function in noninstitutionalized older adults aged 65 years to 80 years [85]. Moreover, a 4-month supplementation regimen of 60 IU to 800 IU vitamin E daily had no adverse effects on various health parameters, including general health, nutrient status, liver enzyme function, thyroid hormone concentrations, creatinine concentrations, serum autoantibodies, killing of *Candida albicans* by neutrophils, and bleeding time in healthy participants older than 65 years [86]. In another randomized controlled trial, older adults consuming 200 mg/d of vitamin E for 4 months exhibited an increase in delayed-type hypersensitivity skin response and an elevation in antibody titer to hepatitis B [87].

Following the review of the literature, a supplementation regimen of 200 mg per day for 6 months was selected. Although no published human studies have reported any serious adverse effects attributed to tocotrienols, it is worth noting that, in animal studies, tocotrienol doses of 500 mg/kg body weight and 1000 mg/kg body weight (administered orally) were found to increase bleeding and clotting times in mice during subacute (14 days) and subchronic (42 days) investigations [88]. When these doses are converted to a human equivalent dose, they equate to 2400 mg and 4800 mg, respectively in humans. This discovery implies that high doses of tocotrienols (>2400 mg) should be used cautiously, particularly by individuals with a tendency to bleed or those taking anticoagulants. Consequently, individuals who are currently on anticoagulant or antithrombotic medication are ineligible for participation in this research.

Although several human studies have explored the potential benefits of tocotrienols, there is a noticeable lack of published, comprehensive data that substantiate their advantages specifically in older adults. To address this knowledge gap, we designed a randomized, double-blind, placebo-controlled study, also widely recognized as the “gold standard” in intervention research [89]. This research design excels in establishing causal relationships, enabling us to demonstrate the efficacy of tocotrienols, compared with placebo, in older adults. The connection between oxidative stress, chronic low-grade inflammation, and the aging process, as well as age-related diseases, has been firmly established through extensive epidemiological studies involving older adults [90]. Consequently, several key investigative areas, including antioxidant and inflammation levels, arterial stiffness, appetite regulation, skin parameters, cognitive functions, and bone mineral density, were chosen as focal points for this research. Tocotrienol supplementation is predicted to have a positive impact on all of these parameters, adding to the increasing amount of data that demonstrates its ability to improve general quality of life of older adults. In particular, tocotrienols have been demonstrated to attenuate arterial stiffness [91], modulate hormones related to appetite [92], improve skin health through improvements in hydration and elasticity [93], promote cognitive performance through neuroprotective mechanisms [11,94], lower oxidative stress and pro-inflammatory markers [95,96], and positively influence bone metabolism [65].

The objective of this randomized, double-blinded, placebo-controlled study is to evaluate the efficacy of TRF supplement on health indices for older adults who have been reported to be at risk of reduced antioxidant levels and low-grade chronic inflammation, factors that contribute to an increased susceptibility to chronic diseases [97]. This study design offers the advantage of establishing causality by assessing the efficacy of TRF compared with placebo in older adults. The outcomes of this trial will provide crucial insights into the potential benefits of TRF supplements for enhancing the health and well-being of older adults.

### Aim of This Study

The comprehensive objectives of this research involve the evaluation of the effectiveness of TRF at enhancing antioxidant levels and reducing inflammation among individuals aged 50 years to 75 years. Furthermore, changes in appetite hormones, arterial stiffness, and skin parameters over 3-month and 6-month supplementation periods are monitored relative to baseline measurements. In addition, alterations in bone mineral density following 6 months of tocotrienol supplementation are being determined, and potential enhancements in cognitive function between baseline and the 6-month point are being investigated. Finally, the influence of supplementation on vitamin E levels within the body is being assessed after 3 months and 6 months of TRF supplementation.

## Methods

### Study Setting

Healthy men and women aged between 50 years and 75 years are recruited from the Klang Valley, which is centered in the federal territories of Kuala Lumpur and Putrajaya in Malaysia. Participants are divided into two cohorts, which are supplemented with either placebo or tocotrienols for 6 months.

### Ethical Considerations

This research upholds the principles of Good Clinical Practice and adheres to the pertinent regulatory guidelines established by the Malaysia Ministry of Health. The research was approved by the Research Ethics Committee of Universiti Kebangsaan Malaysia (ethics approval number: UKM PPI/111/8/JEP-2019-798) and was registered with the Malaysia National Medical Research Register and National Pharmaceutical Regulatory Agency. Funding for the study was provided by KL-Kepong Oleomas Sdn Bhd, with the research itself being independently conducted by scholars and experts from a higher learning institution. Before the clinical trial commenced, the two parties signed a distinct legal agreement designed to safeguard the rights of the sponsor and researchers involved.

The investigators have no financial nor other competing interests in relation to the overall trial, ensuring impartiality and scientific integrity. Any alterations to the protocol are communicated by the investigators to both the Research Ethics Committee and the sponsor prior to implementation.

Upon completion of the trial, the principal investigator (PI) and sponsor will collaborate in publishing the results and deriving pertinent conclusions while ensuring strict confidentiality of participants’ personal information.

The PI is responsible for retaining the data for a minimum duration of 7 years from the date of closure of the database. The sponsor possesses exclusive rights to use the data for commercial purposes, except for any personal information related to the participants. Concurrently, researchers are granted the privilege to use the data for noncommercial purposes, encompassing but not limited to patient care and treatment, academic pursuits, and publication.

Special ethical considerations have been addressed in accordance to the specific needs of the older adult participants in this study. Given the possibility of age-related cognitive decline, the informed consent process incorporates simplified language and comprehension testing to assure accurate understanding. Extra care is taken to reduce any psychological pain or stigmatization, and cognitive examinations are carried out using validated instruments suitable for older adults. All study procedures are intended to accommodate physical or emotional weaknesses, including flexible scheduling and participant comfort during data collection. Throughout the research process, these safeguards maintain each participant's autonomy, dignity, and safety. The eligible participants were compensated RM 40 (US $9.48) for each visit.

### Eligibility Criteria

Participants in this research must meet specific health criteria, including being generally healthy as determined using physical examination and lab-based blood tests, with satisfactory liver and renal function tests. Eligible participants can be of either gender and aged between 50 years and 75 years. They should not be allergic to palm oil and vitamin E and should not have consumed vitamin E or any other antioxidant supplements in the past 3 months. Furthermore, they must be willing and able to adhere to the study’s visit schedule and procedures, reside within a geographically feasible proximity for adequate follow-up (as determined by the investigator), and have a clear understanding of the study protocol, as indicated by their signed informed consent forms.

Participants in this study are expected to reflect greater distribution among the Malay and Chinese population, as these two races are the majority in Malaysia. Meanwhile, participation from the Indian community is less expected as they avoid bovine-related products in their dietary consumption due to religious reasons, aside from being the minority in the country. Moreover, the gender distribution is expected to be balanced between both men and women as there were 2 million individuals of each gender in people aged 60 years and older as of the 4th quarter of 2024 [10]. The socioeconomic background of the participants (ie, education background, occupation, and social status) is not entirely restricted as we intend to be inclusive of all population groups, aside from factoring in the limited availability of participants. However, we note that the participants’ education background may influence cognitive performance before and after supplementation. Thus, we will record their academic background when performing the assessments for cognitive function.

Participation in this research is restricted based on several exclusion criteria, such as individuals with fat malabsorption. This is because tocotrienols, as fat-soluble compounds, require adequate lipid absorption to achieve maximum bioavailability. In addition, those with chronic conditions such as cardiac diseases, neurological diseases, diabetes, HIV infection, or psychiatric illness or social situations are not eligible because these conditions and their associated treatments may have an impact on the study end points by obscuring the specific effects of tocotrienol supplementation.

Individuals following a vegan diet are also excluded due to potential nutritional differences, particularly in fat intake and fat-soluble vitamin levels, which may alter tocotrienol absorption and metabolism. Moreover, those who have smoked within the past 3 months are also excluded since smoking can cause oxidative and systemic stress, which can alter overall inflammation, vascular function, and antioxidant status. Excluding people who have recently undergone or are planning for surgery may be helpful to eliminate confounding side effects from surgical stress and postoperative drugs. Furthermore, pregnant and lactating women are excluded for ethical and safety reasons, given the lack of data on tocotrienol use in these populations. Individuals with a history of bleeding disorders, liver dysfunction, or gastrointestinal ulcers (eg, thrombocytopenia, abnormal liver function, liver diseases such as chronic hepatitis, gastrointestinal ulcers) are also excluded due to the potential risk of bleeding complications as well as reduced tocotrienol metabolism and clearance. Participants who are taking antibiotics, anticoagulants, antithrombotics, or other supplements that may interact with tocotrienol activity are excluded to avoid pharmacological interactions that could compromise research safety or supplementation efficacy.

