### Analyses

Statistical analysis is conducted using SPSS (IBM Corp). The Kolmogorov-Smirnov test will be performed to assess the normality of the data distribution. Type III sum of squares is set to evaluate the hypotheses.

A mixed-design ANOVA will be used to determine whether supplementation affects the blood biochemistry parameters (inflammation and oxidative stress) and physical health (body composition, skin, cognitive function, and vascular health) at baseline, 3 months, and 6 months among the groups. The Mauchly test of sphericity will be conducted to assess homogeneity of variance and compare the means of the supplemented group with those of the placebo group. To account for the risk of a Type I error as a result of many primary and secondary outcomes, multiplicity correction procedures will be used. In particular, the Benjamini-Hochberg approach for false discovery rate control will be used in each outcome domain (eg, oxidative stress markers, inflammatory markers, cognitive tests). Statistical power and Type I error control are balanced for exploratory research in this method with connected variables. The Tukey post hoc test will be used for comparisons between groups, while the Dunnett test will be used for comparisons within groups over time. In terms of missing data, linear mixed-effects models with the missing at random assumption will be used, which is acceptable given the repeated-measures design and inclusion of observed predictors. Nevertheless, dropout rates in older adult groups might differ from missing at random (for example, because of undetected health decline). To evaluate the possible impact of data missing not at random, sensitivity analyses will be conducted using pattern-mixture models and multiple imputation with delta-adjustment scenarios. These methods aid with determining the robustness of the findings under alternate missingness assumptions. All data will be presented as mean (SD), with statistical significance defined as *P*<.05.

This study requires a total of 220 volunteers as calculated using the power and sample size program. In the case where any participant withdraws or is eliminated during the course of the project, their ID number is not reused. Instead, new volunteers are recruited to maintain the total sample size at 220. The distribution of the IP numbers is rerandomized and adjusted as needed to ensure that both groups remain equally balanced, with 110 participants receiving each IP.

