### Monitoring

Participants are instructed to maintain their regular lifestyle throughout the study duration. We recommend that they adhere to their usual routine regarding the number of meals and dietary plan. If there is a need to use any medication, they are required to inform the PI to ensure proper documentation in the CRF.

To ensure compliance, participants are requested to submit the provided supplement bottles during their visits at 3 and 6 months. The percentage of the leftover supplements in the returned bottles are used to track compliance. The purpose of these data is to evaluate intervention adherence. To account for adherence-related differences in the treatment effect, the compliance percentage is incorporated as a covariate in the statistical analyses. Additionally, subgroup analyses based on adherence levels (high, medium, and low compliance) will be carried out.

Additionally, plasma vitamin E levels are measured at 0, 3, and 6 months to assess the participants’ response to supplementation. In the event of suspected side effects or adverse reactions, participants should promptly report to the PI and seek immediate medical assistance. The PI must assess whether the observed effects are related to the trial and determine if the participant should be excluded from the study accordingly.

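### Education is recorded because it may affect cognitive scores, but the stated cognitive analysis gives it no role; a baseline-and-education ANCOVA would be modestly more precise

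*Protocol article*

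**What the plan says.** **Education.** Under Eligibility Criteria the protocol article leaves socioeconomic background, including education, largely unrestricted. It notes that "participants’ education background may influence cognitive performance before and after supplementation" and concludes that "we will record their academic background when performing the assessments for cognitive function". It does not say what the recorded variable will be used for.

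**Cognitive analysis.** The Analyses section states: "A mixed-design ANOVA will be used to determine whether supplementation affects the blood biochemistry parameters (inflammation and oxidative stress) and physical health". Physical health there covers "body composition, skin, cognitive function, and vascular health) at baseline, 3 months, and 6 months among the groups". No baseline covariate is named. Outcomes and Table 1 place the MoCA, RAVLT and digit span at 0 and 6 months only, so for these tests the time factor has two levels. Cognition is a secondary outcome.

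**Covariates named elsewhere.** Monitoring says that "the compliance percentage is incorporated as a covariate in the statistical analyses". In the missing-data text, the Analyses section calls the missing-at-random assumption "acceptable given the repeated-measures design and inclusion of observed predictors", without listing the predictors.

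**Allocation.** Assignment of Interventions describes 1:1 allocation in blocks of 60 and no stratification factor.

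**The concern.** The article gives a reason to collect education that is specific to cognition, then describes the cognitive analysis without it. The one covariate it does name is adherence, which is measured after randomization and cannot stand in for a baseline prognostic factor.

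Two things are at stake, both modest:
- **Precision.** In a two-visit mixed-design ANOVA, the treatment test is the group-by-time interaction, which is a comparison of mean change. With equal variances at the two visits, that is less efficient than comparing month-6 scores adjusted for baseline. Once baseline is adjusted for, education can still explain some of what remains.
- **Chance imbalance.** Allocation is not stratified by education, so the arms may differ on it by chance. Where education predicts change, an unadjusted contrast carries that difference.

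**Working it through.** The plan has no figure of its own to reproduce here: its sample size rests on LDL, and it gives no correlation for any cognitive test. The correlations below are assumptions, shown as ranges.

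**Inputs**
- 110 per arm (Sample Size).
- Cognition measured at 0 and 6 months (Outcomes, Table 1).
- Assumed: equal variance (set to 1) at both visits; pre-post correlation ρ = 0.5 to 0.8; education correlated r = 0.2 to 0.5 with the score, equally at both visits.

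**Step 1: education in the planned contrast.** The covariance of education with change is r − r = 0, so adding education leaves the standard error unchanged (factor 1.000). A simulation of 2,000 trials with 110 per arm, ρ = 0.7 and r = 0.4 gave a mean standard error of 0.1042 without education and 0.1045 with it. A chance imbalance in education cancels here for the same reason. Education helps this contrast only if it predicts change. At an assumed correlation of 0.1 to 0.3 with change, it would remove r² = 1 to 9% of the variance.

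**Step 2: change contrast versus ANCOVA on baseline.**
- Variance of change: 2(1 − ρ)
- Residual variance after baseline adjustment: 1 − ρ²
- Ratio: (1 − ρ²) / [2(1 − ρ)] = (1 + ρ)/2

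At ρ = 0.5 the ratio is 0.75, and at ρ = 0.8 it is 0.90. Baseline adjustment therefore cuts variance by 25% and 10% respectively. In the same simulation (ρ = 0.7) the standard error fell from 0.1042 to 0.0963. The squared ratio is 0.85, which matches (1 + 0.7)/2.

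**Step 3: education added to that ANCOVA.** The further proportional fall in residual variance is the squared partial correlation:

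r²(1 − ρ) / [(1 + ρ)(1 − r²)]

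At ρ = 0.7 and r = 0.4 this is 0.16 × 0.3 / (1.7 × 0.84) = 0.048 / 1.428 = 3.4%.

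| ρ | r = 0.2 | r = 0.3 | r = 0.4 | r = 0.5 |
|---|---|---|---|---|
| 0.5 | 1.4% | 3.3% | 6.3% | 11.1% |
| 0.6 | 1.0% | 2.5% | 4.8% | 8.3% |
| 0.7 | 0.7% | 1.7% | 3.4% | 5.9% |
| 0.8 | 0.5% | 1.1% | 2.1% | 3.7% |

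On the standard-error scale the factor runs from 0.998 down to 0.943.

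**Step 4: both together.** The joint variance ratio runs from 0.90 × (1 − 0.005) = 0.90 (ρ = 0.8, r = 0.2) to 0.75 × (1 − 0.111) = 0.67 (ρ = 0.5, r = 0.5). In the first case nearly all of the gain comes from baseline, and in the second most of it does.

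**Step 5: size of a chance imbalance.** The between-arm difference in mean education, in SD units, has standard deviation √(2/110) = 0.135, so its 95% limits are ±1.96 × 0.135 = ±0.26 SD.

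**The case against.** **The article does not say that education will go unused.** This stands. The mixed-model text mentions observed predictors without listing them, and an analysis plan that is not shown may name education. A reader might infer that the trial will discard the variable, or that the model contains arm and time only. The documents support neither: compliance is named as a covariate, and the predictor list is open. The narrower statement does hold. Education is given no analytic role in the text, although the article goes into covariates, post hoc tests, multiplicity and sensitivity analyses. The mention of predictors is there to justify an assumption about missing data, so it does not settle the treatment comparison.

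**A stable education effect is not in the error term of the planned test.** This also stands (Step 1). A reader might infer that leaving education out inflates the error of the planned cognitive comparison. That follows only if education predicts change, and the article gives no evidence or size for that. A comparison of month-6 scores that ignored baseline would lose more (standard-error factor √(1 − r²), or 0.980 to 0.866 for r = 0.2 to 0.5), but that is not the model described.

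**Randomization already protects the comparison.** Correct. Without stratification or adjustment the estimate is still unbiased. Adjustment allows for a chance imbalance; it does not create balance.

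**The gain belongs to a different model from the one planned.** True. The recommendation changes the model as well as adding a covariate, and most of the benefit comes from the change of model. That is a reason to describe the two gains separately, as above, and not a reason to forgo them.

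**Conclusion.** The point holds as a minor improvement to the analysis of secondary outcomes. The planned cognitive comparison is valid and unbiased, and nothing here shows that a conclusion would change. It does leave a recorded baseline factor, which the article itself calls influential, without a stated role, and it uses a less efficient contrast than the data allow.

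Under the assumed correlations, baseline adjustment lowers variance by about 10 to 25% relative to the change contrast, and education lowers the remaining residual variance by a further 0.5 to 11%. These sizes rest on equal variances at the two visits and an education effect of the same size at both. If education also predicts retest change, its contribution would differ, and the planned contrast would then gain from it too.

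**What to change.** Before unblinding, state in the Analyses section that month-6 MoCA, RAVLT and digit span scores will be compared between arms by ANCOVA, with arm, baseline score and education as terms, and fix the coding of education (years, or named levels) in advance.

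If a linear mixed model is preferred, so that the missing-data approach is the same, baseline must enter as a covariate or the arms must be constrained to a common baseline mean. Education should be allowed a separate effect at each visit. An unconstrained group-by-time model with complete data simply returns the change contrast. Naming education among the observed predictors would also make the missing-at-random assumption easier to judge.

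The Results section reports that data from the first 120 participants have already been analyzed, so the addition should be dated and should record that it was made without knowledge of which product each group received.

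The cost is a few lines of text and one degree of freedom for years of education, or a few for levels. No new data are needed.
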